### **13.3 CTEPH/non-CTEPH determination in the secondary endpoint (pulmonary circulation analysis program images)**

For one secondary endpoint, the same five readers as in the primary endpoint will interpret dynamic chest radiography/pulmonary circulation analysis images in the intervention group to determine CTEPH/non-CTEPH. In this evaluation, the determination will be made by majority vote among the five readers.

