**5.7.2 Secondary endpoints**

- Comparison of sensitivity, specificity, positive predictive value and negative predictive value for initial discrimination between CTEPH and non-CTEPH between the group of the standard initial work-up alone versus the device -added group in the ITT population.
- Agreement (kappa coefficient) between the pulmonary circulation analysis program and perfusion scintigraphy regarding the presence of regional perfusion defects in each of six lung regions.

[figure not shown][figure not shown][figure not shown]

| Right                                    | Left                                     |
|------------------------------------------|------------------------------------------|
| Upper:
Perfusion defect
( + / - )  | Upper:
Perfusion defect
( + / - )  |
| Middle:
Perfusion defect
( + / - ) | Middle:
Perfusion defect
( + / - ) |
| Lower:
Perfusion defect
( + / - )  | Lower:
Perfusion defect
( + / - )  |

| Right                                              | Left                                               |
|----------------------------------------------------|----------------------------------------------------|
| Upper:
Segmental perfusion defect
( + / - )  | Upper:
Segmental perfusion defect
( + / - )  |
| Middle:
Segmental perfusion defect
( + / - ) | Middle:
Segmental perfusion defect
( + / - ) |
| Lower:
Segmental perfusion defect
( + / - )  | Lower:
Segmental perfusion defect
( + / - )  |

[figure not shown]

Kappa coefficient for agreement in six area

- Performance evaluation of dynamic chest radiography/pulmonary circulation analysis program for discriminating CTEPH versus non-CTEPH using perfusion scintigraphy as the reference standard: sensitivity, specificity, accuracy, PPV and NPV, in accordance with the STARD 2015 guideline.

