### **13.2 Determination of CTEPH/non-CTEPH in the primary endpoint**

For the primary endpoint, five internal medicine physicians will perform the initial discrimination between CTEPH and non-CTEPH in each reading group (standard initial work-up group and standard initial work-up plus pulmonary circulation analysis program group). The five readers in each group will include three readers with more than five years of experience in CTEPH diagnosis and two readers with five years or less of experience.

For the primary endpoint, the adopted interpretation will not be decided by a simple majority vote. Instead, a prespecified correspondence table will be created in advance such that a single reader's judgement is uniquely adopted for each case. Readers will not be informed of which cases constitute the primary endpoint analysis set.

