### **13.4 Determination of regional perfusion defects (six-region assessment)**

For the six-region assessment, each lung is divided into upper, middle and lower regions (six regions in total). Each region will be assessed for the presence or absence of a perfusion defect on pulmonary circulation analysis images and on perfusion scintigraphy images.

Pulmonary circulation analysis images will be interpreted by the same five internal medicine physicians as in the intervention group. Perfusion scintigraphy images will be interpreted by three nuclear medicine physicians from CTEPH expert centres. All designated readers will interpret all cases. The final presence/absence of a regional perfusion defect for each region will be determined by majority vote.

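### The device-versus-scintigraphy measures and the six-region kappa are scored on a five-reader majority vote, so they estimate panel performance rather than that of one clinician using the device

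*Protocol*

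**What the plan says.** Protocol section 5.7.2 has two secondary endpoints that describe the device itself.

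- The first of these is "Agreement (kappa coefficient) between the pulmonary circulation analysis program and perfusion scintigraphy" in six lung regions.
- The second is CTEPH discrimination by the device "using perfusion scintigraphy as the reference standard: sensitivity, specificity, accuracy, PPV and NPV".

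Section 13 fixes how the calls behind them are made.

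- **Device CTEPH call (13.3):** "the same five readers as in the primary endpoint will interpret dynamic chest radiography/pulmonary circulation analysis images in the intervention group". Then: "In this evaluation, the determination will be made by majority vote among the five readers".
- **Six-region score (13.4):** "Pulmonary circulation analysis images will be interpreted by the same five internal medicine physicians as in the intervention group". On the comparator side, "Perfusion scintigraphy images will be interpreted by three nuclear medicine physicians from CTEPH expert centres". For both modalities, "The final presence/absence of a regional perfusion defect for each region will be determined by majority vote".
- **Primary endpoint (13.2), by contrast:** "the adopted interpretation will not be decided by a simple majority vote". A table prepared in advance picks one reader's call for each case.

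Section 13.5 calls for an assessment of variability between readers of the device images. Subanalysis 1 in section 5.7.3 compares the two reading groups by reader experience. Neither names a reader-level or reader-averaged sensitivity, specificity or kappa against scintigraphy.

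**The concern.** Section 1.3 presents the device as a tool for clinicians in non-expert centres who must judge how urgent a referral is. Nothing there describes five physicians voting. The primary endpoint respects this by scoring one reader per case, yet the two endpoints that characterise the device do not.

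A majority vote removes those errors that readers do not share. How much it removes depends on how strongly their errors are correlated, and a majority result alone does not show that. If the rule is followed as written, the report will give device sensitivity, specificity and kappa that belong to a panel. A reader of the report could take them as what one clinician can expect.

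**Working it through.** **The plan's own figure.** The protocol gives no figure for the majority-vote endpoints. Its only related calculation is the primary sample size (section 10.1), which reproduces. With accuracies 0.705 and 0.92 (mean 0.8125), two-sided 5% and 80% power:

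n = [1.960 × √(2 × 0.8125 × 0.1875) + 0.842 × √(0.705 × 0.295 + 0.92 × 0.08)]² / 0.215² = (1.082 + 0.447)² / 0.0462 ≈ 50.5, so 51 per group and 102 in total.

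102 / 0.95 = 107.4, so 108. This point does not touch that result.

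**Inputs from the protocol.** Five device readers, at least three of five needed (13.3, 13.4); three scintigraphy readers (13.4).

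**Assumed inputs, not in the protocol.** Single-reader rate p, between-reader correlation ρ, and region-level prevalence, sensitivity and specificity.

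**Step 1, independent errors.** P(at least 3 of 5 correct) = Σ C(5,x) pˣ (1−p)⁵⁻ˣ for x = 3 to 5. At p = 0.80: 0.2048 + 0.4096 + 0.3277 = 0.942.

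**Step 2, correlated errors.** Beta-binomial with a = p(1−ρ)/ρ and b = (1−p)(1−ρ)/ρ: P = Σ C(5,x) B(x+a, 5−x+b) / B(a,b) for x = 3 to 5.

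| Single reader | ρ = 0 | ρ = 0.2 | ρ = 0.4 | ρ = 0.8 |
|---|---|---|---|---|
| 0.80 | 0.942 | 0.872 | 0.833 | 0.803 |
| 0.85 | 0.973 | 0.916 | 0.881 | 0.853 |

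At 0.80 the gain runs from 0.942 − 0.80 = 0.142 down to 0.803 − 0.80 = 0.003.

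**Step 3, kappa.** The scintigraphy majority is held as the comparator. Assume region prevalence 0.375, single-reader sensitivity 0.75 and specificity 0.90.

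- Observed agreement: 0.375 × 0.75 + 0.625 × 0.90 = 0.844.
- Share called positive: 0.375 × 0.75 + 0.625 × 0.10 = 0.344.
- Chance agreement: 0.375 × 0.344 + 0.625 × 0.656 = 0.539.
- Single-reader kappa: (0.844 − 0.539) / (1 − 0.539) = 0.66.

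Applying steps 1 and 2 to sensitivity and specificity gives a panel kappa of 0.90, 0.79, 0.72 and 0.67 at ρ = 0, 0.2, 0.4 and 0.8.

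**Step 4, where the direction fails.**

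- *Shared hard cases.* Let 70% of cases be easy (p = 0.95) and 30% hard (p = 0.30). Single reader: 0.7 × 0.95 + 0.3 × 0.30 = 0.755. Majority: 0.7 × 0.9988 + 0.3 × 0.1631 = 0.748.
- *One measure below 0.5.* A single-reader sensitivity of 0.40 becomes 0.317 under an independent majority, whatever the overall accuracy.
- *One strong reader.* With one reader at 0.95 and four at 0.70, independent, the majority is 0.95 × 0.9163 + 0.05 × 0.6517 = 0.903, below the best reader.

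**The case against.** The best defence is that these endpoints ask how well the images agree with scintigraphy, not how one clinician performs. A pooled read is a recognised choice for that question, and the retrospective study in section 1.5 used two-reader consensus on both modalities. Single-reader evidence already comes from the primary endpoint and from the between-group sensitivity, specificity, PPV and NPV. Section 13.5 does look at reader variability. All readers see the same images after the same training, so high correlation and a small gain are credible. Finally, the size of the effect is wholly assumed.

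Much of this stands, and it limits the point to secondary endpoints. It does not remove it. The between-group measures score the work-up plus device images, not the device against scintigraphy. Variability among readers is not accuracy against a comparator. The voting rule is fixed in the protocol itself, so it is not a detail left open for the SAP.

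Three stronger readings are tempting, and the documents do not support them.

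- **That the panel figures must overstate single-reader performance whenever accuracy exceeds 0.5, or must beat every individual reader.** The counterexamples in step 4 rule out both. Table 1 gives the device coarser spatial resolution than scintigraphy, so defects missed by most readers are plausible. Section 13.2 also mixes experience levels, so one reader may well beat the panel.
- **That the vote is what prevents comparison with the primary result.** The primary endpoint uses work-up plus images and is judged against the investigator's diagnosis. This endpoint uses device images and is judged against perfusion scintigraphy. Inputs and reference both differ, so changing the vote would not make them comparable.
- **That the primary conclusion is compromised.** Section 13.2 adopts one reader per case, so it is not.

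**Conclusion.** The point holds as a matter of what is being estimated. Followed as written, sections 13.3 and 13.4 deliver panel performance only, for both endpoints that describe the device. Inflation relative to the average single reader is likely but not certain, and its size cannot be derived from the protocol. Under exchangeable readers at 0.80, the accuracy gain is about 0.14 with independent errors, 0.03 to 0.07 at correlation 0.4 to 0.2, and almost nothing at 0.8. In the kappa example, 0.66 rises by 0.24 with independent errors, by 0.06 to 0.13 at correlation 0.4 to 0.2, and by 0.01 at 0.8. Where most readers miss the same cases, the sign can reverse. These sizes rest on assumed accuracies, prevalence and correlations. The primary endpoint, the between-group secondary comparisons and the sample size are unaffected. This is a worthwhile improvement to secondary endpoints, not a flaw in the trial's main test.

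**What to change.** In sections 13.3 and 13.4, prespecify the following before reading results are available.

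1. **Main estimate.** Compute each measure separately for each of the five device readers against the comparator, then average over readers. Use an interval that allows for clustering by case and reader, for example a bootstrap or GEE. For kappa, keep the six regions of a case together.
2. **Spread.** Show the range across the five readers.
3. **Supportive result.** Keep the five-reader majority, labelled as panel performance.
4. **Comparator.** Keep the three-reader scintigraphy majority, which is reasonable for a reference.

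No new reads, patients or sites are needed. A five-reader vote already requires five individual calls, and section 13.4 has every designated reader read every case. The cost is a change of wording, some programming and probably less favourable device figures.

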### **13.4 Determination of regional perfusion defects (six-region assessment)**

For the six-region assessment, each lung is divided into upper, middle and lower regions (six regions in total). Each region will be assessed for the presence or absence of a perfusion defect on pulmonary circulation analysis images and on perfusion scintigraphy images.

Pulmonary circulation analysis images will be interpreted by the same five internal medicine physicians as in the intervention group. Perfusion scintigraphy images will be interpreted by three nuclear medicine physicians from CTEPH expert centres. All designated readers will interpret all cases. The final presence/absence of a regional perfusion defect for each region will be determined by majority vote.

### **13.5 Reader training**

Prior to the start of image interpretation, readers will undergo training on how to interpret pulmonary circulation analysis images. After training, each reader will perform a test interpretation to confirm that the reader has acquired the necessary interpretation skills. The committee will evaluate inter-reader variability of pulmonary circulation analysis images.

## **14 Record retention**

### **14.1 Retention of essential documents by implementing medical institutions**

Implementing medical institutions will retain essential documents related to the trial until the later of: (i) the date of marketing approval for the application for approval of the investigational device in which this trial data are used, or three years after notification of termination of development if development is discontinued; and (ii) three years after trial completion or trial termination.

The head of each implementing medical institution will appoint a person responsible for record retention to retain the documents and will take all necessary measures to prevent loss or damage. The documents must be available for inspection upon request.

### **14.2 Retention by the institutional review board (IRB)**

The IRB of each implementing medical institution will retain essential documents related to the trial until the later of: (i) the date of marketing approval for the application for approval of the investigational device in which this trial data are used, or three years after notification of termination of development if development is discontinued; and (ii) three years after trial completion or trial termination.

### **14.3 Retention by the coordinating investigator**

The coordinating investigator will retain essential documents related to the trial until the later of: (i) five years after the date of marketing approval for the application for approval of the investigational device in which this trial data are used, or three years after notification of termination of development if development is discontinued; and (ii) three years after trial completion or trial termination.

The coordinating investigator will promptly notify principal investigators at implementing medical institutions when marketing approval has been obtained and/or when the retention period has elapsed.

## **15 Quality control and quality assurance**

### **15.1 Quality control**

The coordinating investigator, principal investigators, subinvestigators and study staff will conduct quality control activities to ensure that the trial is conducted appropriately and that the data are reliable, in accordance with applicable laws and regulations and the trial SOPs.

### **15.2 Monitoring**

Monitoring will be conducted in accordance with the Monitoring SOP. Monitoring will include on-site and/or off-site procedures, as appropriate, to confirm that the trial is conducted safely and in compliance with the protocol, applicable regulations, and Good Clinical Practice for medical device trials, and that the data recorded are accurate and complete.

### **15.3 Audit**

Audits are planned to be conducted at least once annually. At the time of protocol Version 3.2, a detailed Audit SOP has not yet been finalised; however, audits will be performed by personnel independent of the conduct and monitoring of the trial, and will assess compliance with the protocol and applicable regulatory requirements. The Audit SOP will be prepared before the first audit is conducted.

### **15.4 Direct access**

The principal investigator will permit direct access to source documents and other trial-related records by monitors, auditors and regulatory authorities as required, while ensuring protection of personal information.

## **16 Ethical considerations**

### **16.1 Applicable ethical principles and regulations**

This trial will be conducted in accordance with the Declaration of Helsinki (revised October 2013), the Pharmaceuticals and Medical Devices Act and related regulations, the Ministerial Ordinance on Good Clinical Practice for Medical Devices (GCP), and the Ethical Guidelines for Medical and Biological Research Involving Human Subjects, as well as other applicable laws and institutional regulations.

### **16.2 Institutional review board (IRB)**

Prior to trial initiation at each implementing medical institution, the protocol, informed consent documents and other relevant materials will be reviewed and approved by the IRB. The IRB will conduct continuing review as required. If new information becomes available that may affect subject safety or willingness to continue participation, the principal investigator will promptly report such information to the head of the implementing medical institution and to the IRB.

### **16.3 Protection of personal information**

The principal investigator will take appropriate measures to protect personal information of subjects in accordance with applicable laws and institutional policies. In particular:

- Subjects will be managed using subject identification codes, and personal identifiers will not be included in data provided outside the implementing medical institution.
- Personal information will be stored in a manner that prevents unauthorised access, leakage, loss or damage.
- When images and data are transferred to the image interpretation committee or other parties, personal information will be masked and de-identified.

### **16.4 Protocol compliance and amendments**

The principal investigator and subinvestigators will conduct the trial in compliance with this protocol. If amendments to the protocol are necessary, the coordinating investigator will

prepare a revised protocol and obtain approval from the head of the implementing medical institution and the IRB as required before implementation.

### **16.5 Protocol deviations**

The principal investigator must not deviate from the protocol without prior approval of the head of the implementing medical institution and the IRB, except when necessary to eliminate an immediate hazard to subjects. Any deviations will be documented, and the reasons and details will be reported to the head of the implementing medical institution and the IRB.

## **17 Informed consent**

### **17.1 Explanation to subjects**

The principal investigator or subinvestigator will explain the following items to the subject using the informed consent document, and will obtain written informed consent before the subject participates in the trial:

- The purpose of the trial.
- The expected duration of participation.
- The trial procedures and the types of examinations to be performed.
- That the trial involves additional imaging (dynamic chest radiography) and associated radiation exposure.
- The reasonably foreseeable risks and inconveniences.
- The expected benefits to the subject and/or others.
- Alternative procedures or treatments that might be available.
- That participation is voluntary and the subject may withdraw consent at any time without disadvantage.
- How confidentiality and protection of personal information will be ensured.
- How trial-related injury will be handled and what compensation is available.
- Any costs to the subject and any reimbursements (if applicable).
- Contact information for questions about the trial and about subject rights.
- That the results may be published and that personal identity will not be disclosed.
- That source documents may be directly accessed by monitors, auditors and regulatory authorities as required.
- That new information that may affect willingness to continue will be provided.

- Any other information required by applicable regulations and institutional policies.

## **17.2 Obtaining consent**

After sufficient explanation, if the subject (or legally acceptable representative, if applicable) agrees to participate, the subject will sign and date the informed consent form. The person obtaining consent will also sign and date the form. A copy of the signed informed consent form will be provided to the subject, and the original will be retained at the implementing medical institution.

## **17.3 Re-consent**

If new information becomes available during the trial that may affect a subject's willingness to continue participation, the subject will be informed promptly. If necessary, revised informed consent documents will be prepared and approved by the IRB, and re-consent will be obtained.

## **18 Conflict of interest**

All personnel involved in this trial will disclose required information to the conflict of interest committee established at their institution in accordance with institutional regulations, and will obtain review and approval.

## **19 Trial costs and compensation**

### **19.1 Funding source**

This trial will be conducted with support from KONICA MINOLTA, INC. The trial is funded by a grant from the Japan Agency for Medical Research and Development (AMED) and by research funding provided by KONICA MINOLTA, INC. to Kyushu University.

### **19.2 Trial-related costs**

Costs for examinations and tests that are normally performed as part of routine clinical care will be handled as part of usual medical expenses covered by health insurance. Any additional examinations required solely for this trial, including dynamic chest radiography, will be handled in accordance with the regulations of each implementing medical institution. Details of cost handling will follow the institutional rules and will be explained to subjects in the informed consent process.

### **19.3 Compensation for health injury**

Because the intervention in this trial is dynamic chest radiography, which is a non-invasive imaging examination with radiation exposure comparable to standard chest radiography, the risk of health injury is considered minimal. Nevertheless, if a subject suffers health injury that is judged to be related to participation in this trial, appropriate medical care and compensation will be provided in accordance with the relevant laws, regulations, and institutional policies. Insurance may be arranged as necessary.

## 19.4 Reimbursement / burden reduction fee

Payment of any burden reduction fee (reimbursement) to subjects will be made in accordance with the regulations of each implementing medical institution.

## 20 Dissemination of results

Results obtained in this trial will belong to Kyushu University Hospital. Information on this trial will be registered and disclosed in clinical trial databases such as the Japan Registry of Clinical Trials (jRCT) and ClinicalTrials.gov prior to trial initiation.

Academic presentations related to this trial may be made by the coordinating investigator or by persons who have obtained approval from the coordinating investigator.

